The first-trimester prediction model developed by the Fetal Medicine Foundation (FMF), integrating maternal factors, mean arterial pressure (MAP), uterine artery pulsatility index (UtAPI), and PlGF, identifies approximately 90% of early preeclampsia (requiring delivery <32 weeks), 75% of preterm preeclampsia (delivery <37 weeks), and 41% of term preeclampsia cases at a 10% screen-positive rate [22]. This approach also detects 56% of early small for gestational age (SGA; delivery <32 weeks) and 46% of preterm SGA (delivery <37 weeks) neonates [23]. Clinical trials have demonstrated that prophylactic aspirin (>100 mg) combined with the first-trimester prediction model effectively prevents preterm preeclampsia and its associated adverse outcomes [24].

Despite these advances, predicting and preventing late-onset or term preeclampsia and FGR remains challenging due to their heterogeneous pathophysiology. These conditions exhibit less pronounced angiogenic biomarker alterations and weaker associations with placental dysfunction than early-onset cases [25]. Although causing fewer adverse outcomes, term complications have a higher prevalence, thus constituting a substantial health care burden [26]. Furthermore, low-dose aspirin appears to be less effective in preventing term preeclampsia [24]. Recent research proposes that risk stratification at 35 to 36 weeks of gestation with planned birth may offer a potential preventive strategy for managing term preeclampsia [27]. However, determining optimal delivery timing based on individualized risk stratification requires more investigation. Emerging evidence links maternal cardiovascular maladaptation and altered hemodynamic profiles with preeclampsia and FGR development, providing new directions for improving prediction models [28,29]. Current research remains limited on combining hemodynamic measurements with placental dysfunction markers to enhance prediction accuracy.

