### Study Objectives

#### Primary Objectives

The primary objectives of this study are as follows:

To improve current predictive models or develop new predictive models for placental dysfunction–related pregnancy complications, including preterm preeclampsia and FGR, at 2 critical gestational periods: the first trimester (11‐13 weeks) and the second trimester (26‐28 weeks)To establish third-trimester (35‐36 weeks) models to predict term preeclampsia and FGR and to define the optimal time for delivery.

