### Definitions of Preeclampsia and FGR

The diagnosis of preeclampsia follows the 2021 International Society for the Study of Hypertension in Pregnancy guideline [31]. Preeclampsia cases are subclassified based on gestational age at delivery as preterm preeclampsia (delivery <37 weeks) or term preeclampsia (delivery ≥37 weeks) [31]. FGR is defined in the absence of congenital anomalies according to international Delphi consensus criteria, with distinctions between early-onset and late-onset presentations (Textbox 1) [32].

Textbox 1.Definitions of early- and late-onset fetal growth restriction [32].

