#### Primary Objectives: Prediction Model Development

Multivariable logistic regression will serve as the primary analytical approach for prediction model development at 3 gestational windows (11‐13 weeks, 26‐28 weeks, and 35‐36 weeks of gestation) to address both primary objectives 1 and 2. Clinically relevant candidate predictors are predefined and entered into multivariable models, followed by model reduction to achieve parsimony (eg, backward elimination with a retention threshold of *P*<.10). Nonlinear relationships between continuous variables and the log odds of the outcomes will be tested with the inclusion of polynomial terms up to the third degree, which will be kept in the model if statistically significant.

For each patient, this method estimates a predicted probability of developing the outcome based on the log odds of the outcome. For primary objective 1, the predicted probabilities can be used to define low- and high-risk subgroups at predefined gestational age thresholds. Specifically, a risk threshold will be defined based on clinically relevant screen-positive rates (eg, 10%, 15%, or 20%) to balance sensitivity and specificity for clinical implementation. For primary objective 2, logistic regression will similarly provide predicted probabilities. In addition, Fine and Gray competing risks time-to-event models will be used as sensitivity analyses accounting for delivery without the outcome of interest (preeclampsia or FGR) as a competing event.

To further improve upon current FMF prediction models, a Bayesian updating approach will be applied to refine existing FMF first-trimester risk estimates using additional biomarkers and clinical variables collected later in pregnancy. The FMF first-trimester risk estimate will be used as the prior probability. Likelihood ratios derived from biomarker and biophysical measurements at 26 to 28 weeks and 35 to 36 weeks will be incorporated via Markov chain Monte Carlo simulations to generate updated posterior risk distributions. This enables dynamic, individualized risk reassessment as pregnancy progresses.

All models will undergo internal validation using 5-fold cross-validation with repeated iterations to obtain stable performance estimates. Model performance will be evaluated using the following metrics:

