## Results

Recruitment for the Placental Health Study commenced in June 2022. By the close of recruitment in February 2026, a total of 1267 participants were enrolled. Of these, 1072 (84.6%) participants had a completed pregnancy, 144 (11.4%) participants are still to complete their pregnancy, and 51 (4%) had withdrawn or with missing or duplicated data. Comprehensive clinical data, including maternal demographics, medical and obstetric history, ultrasound measurements, Doppler indices, hemodynamic parameters, pathology laboratory results, and pregnancy outcomes, were collected through integration with electronic medical records (Table 1). Data were recorded in REDCap. Maternal serum, plasma, whole blood for RNA extraction, and urine samples have been collected and processed according to standardized operating procedures. Biospecimens are stored at −80 °C.

**Table 1. T1:** Summary of data and sample collection throughout pregnancy.

Assessment period and category	Data collected
At enrollment	
Demographic data	Date of birth, age, height, weight, BMI, ethnicity, smoking, and alcohol use status
Medical history	Diabetes mellitus, chronic hypertension, systemic lupus erythematosus, and antiphospholipid syndrome
Obstetric history	Miscarriage, termination, parity, previous preterm birth, preeclampsia, FGR^a^, placental abruption, and placenta previa
Risk assessment	Preeclampsia risk scoring (NICE^b^ and ACOG^c^ guidelines)
11‐13 weeks assessment	
First-trimester risk assessment	NIPT^d^ results (risk of trisomies, fetal sex, risk of monosomy X, sex chromosome aneuploidy risk, 22q11.2 deletion risk, and fetal fraction [cfDNA^e^, %], FGR risk, and preterm preeclampsia risk
Ultrasound and Doppler	Fetal biometry (CRL^f^ and NT^g^), fetal Doppler (ductus venosus A-wave), maternal Doppler (right and left uterine artery PI^h^ and mean PI), biophysical markers (cervical length and measurement method), and ultrasound markers (nasal bone, tricuspid regurgitation, cardiac activity, FHR^i^, holoprosencephaly, diaphragmatic hernia, atrioventricular septal defect, exomphalos, and megacystis)
BP^j^	Systolic BP, diastolic BP, and MAP^k^
Biochemical markers	Free beta-hCG^l^, PAPP-A^m^, PlGF^n^, sFlt-1^o^, and sFlt-1:PlGF ratio
Clinical pathology	Urine test, full blood count, chemistry panel, and recent iron infusion date (if available)
26‐28 and 35‐36 weeks	

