Ultrasound and Doppler	Fetal biometry (BPD^p^, HC^q^, AC^r^, FL^s^, EFW^t^, and DVP^u^); biophysical markers (cervical length and measurement method and placenta position); fetal Doppler (umbilical diastolic flow, UA^v^ PI Dopplers, MCA^w^ PI Dopplers, ductus venosus A-wave, and ductus venosus Dopplers-PIV^x^); and maternal Doppler (right and left uterine artery pulsatility index and mean PI)
Maternal hemodynamics	Systolic BP, diastolic BP, MAP, augmentation index, and maternal ophthalmic artery Doppler (right and left PI, RI^y^, EDV^z^, PSV^aa^-1, PSV-2, and PSV-2:PSV‐1)
Biochemical markers	PlGF, sFlt-1, and sFlt-1:PlGF ratio
Clinical pathology	Urine test, full blood count, chemistry panel, and recent iron infusion date (if available)
GDM screening	Random glucose, HbA_1c_^ab^, OGTT^ac^ (fasting, 1-hour, and 2-hour values); and insulin or metformin use
At delivery	
Delivery details	Gestational age at delivery; onset of labor; type of rupture of membrane; PPROM^ad^; FBS^ae^ test results; delivery type; number of vessels in cord; antenatal, intrapartum, and postnatal blood loss; postpartum hemorrhage
Neonatal outcomes	Live birth or stillbirth, onset of respirations, birth weight, birth length, head circumference, sex, Apgar scores (1 and 5 minutes), resuscitation, cord gas analysis, and SCN^af^ or NICU^ag^ admission
Maternal outcomes	BP, postpartum hemorrhage, and adverse events
All visits	
Pregnancy complication and medication	Preeclampsia, GH^ah^, antepartum hemorrhage, threatened preterm labor, FGR, PPROM, GDM^ai^; gestational age at diagnosis; medication details (start and stop date and dose)
Biological sample collection	Plasma, serum, whole blood (in PAXgene RNA blood tube), and urine

a FGR: fetal growth restriction.

b NICE: National Institute for Health and Care Excellence.

c ACOG: American College of Obstetricians and Gynecologists.

d NIPT: noninvasive prenatal testing.

e cfDNA: cell-free DNA.

f CRL: crown-rump length.

g NT: nuchal translucency.

h PI: pulsatility index.

i FHR: fetal heart rate.

j BP: blood pressure.

k MAP: mean arterial pressure.

l hCG: human chorionic gonadotropin.

m PAPP-A: pregnancy-associated plasma protein A.

n PlGF: placental growth factor.

o sFlt-1: soluble fms-like tyrosine kinase-1.

p BPD: biparietal diameter.

q HC: head circumference.

r AC: abdominal circumference.

s FL: femur length.

t EFW: estimated fetal weight.

u DVP: deepest vertical pocket.

v UA: umbilical artery.

w MCA: middle cerebral artery.

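### The Bayesian update does not tie the first-trimester prior to the outcome being updated, nor make the later likelihood ratios conditional on markers already in that prior

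*Protocol article*

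**What the plan says.** All of this is in the protocol article.

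- **Prior and update** (Primary Objectives: Prediction Model Development). "The FMF first-trimester risk estimate will be used as the prior probability". Then: "Likelihood ratios derived from biomarker and biophysical measurements at 26 to 28 weeks and 35 to 36 weeks will be incorporated", by Markov chain Monte Carlo (MCMC), to give posterior risk distributions. The purpose is to refine the FMF risk "using additional biomarkers and clinical variables collected later in pregnancy". No outcome is named for the prior or the posterior.
- **What the prior contains** (Introduction). The FMF first-trimester model is described as "integrating maternal factors, mean arterial pressure (MAP), uterine artery pulsatility index (UtAPI), and PlGF".
- **Which first-trimester risks are recorded** (Results, Table 1, 11–13 weeks). The disease risks listed are "FGR risk, and preterm preeclampsia risk". No term-preeclampsia risk is listed.
- **What the 35–36 week window is for** (Primary Objectives). It is to establish "models to predict term preeclampsia and FGR and to define the optimal time for delivery".
- **How the two forms of preeclampsia are separated** (Definitions of Preeclampsia and FGR). "preterm preeclampsia (delivery <37 weeks) or term preeclampsia (delivery ≥37 weeks").
- **What is measured again** (Table 1, 26–28 and 35–36 weeks). Maternal hemodynamics comprise "Systolic BP, diastolic BP, MAP, augmentation index, and maternal ophthalmic artery Doppler". Uterine artery PI and PlGF are also listed at both later windows.

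**The concern.** Bayes' rule in odds form gives the risk of an event only when the prior and the likelihood ratios refer to that same event, in the same population, and each ratio is conditional on the information already used. The text secures neither condition.

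**Outcome.** Preterm and term preeclampsia are mutually exclusive by date of delivery. A prior for one cannot be turned into a posterior for the other by any set of likelihood ratios. Where the outcome does match, a woman undelivered and unaffected at a later visit has already passed part of the risk that the first-trimester figure covered.

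**Information.** Repeat readings of one marker in one woman are usually correlated. A ratio computed from the later reading alone, multiplied onto a prior that contains the earlier reading, uses their common part twice. The same applies between the 26–28 and 35–36 week readings.

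At stake is the calibration of the individual risks that this update is meant to deliver, and so any claim that it improves on the FMF estimate.

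**Working it through.** The article gives no figure for the update, so there is nothing to reproduce. Three checks follow.

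**1. Does a recorded prior match each target?**

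| Window | Target (Primary Objectives) | First-trimester risk listed in Table 1 | Match |
|---|---|---|---|
| 26–28 weeks | preterm preeclampsia | preterm preeclampsia | yes |
| 26–28 weeks | FGR | FGR | yes |
| 35–36 weeks | FGR | FGR | yes |
| 35–36 weeks | term preeclampsia | none listed | no |

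One pairing of four lacks a matching prior. The other three still need the prior to refer to women still pregnant and undiagnosed at the visit.

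**2. Size of the mismatch, if the preterm risk were used for term preeclampsia.**

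Inputs from the article: FMF detection of 75% (preterm) and 41% (term) at a 10% screen-positive rate (Introduction); term disease at least twice as frequent as preterm (Discussion). Assumptions: equal-variance binormal model, screen-positive rate taken as the false-positive rate, prior well calibrated for preterm disease, preterm prevalence 0.5–1.5%.

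- Separation d = z(detection) − z(0.10).
- Preterm: 0.674 + 1.282 = 1.956. Term: −0.228 + 1.282 = 1.054.
- Calibration slope of the preterm prior for term disease = 1.054/1.956 = 0.54. Simulation with 1,000,000 women gives 0.53–0.54.
- Observed/expected = term prevalence divided by mean prior. With term twice as frequent, for example, 0.0100/0.00476 = 2.10; the range over the assumed prevalences is 2.10–2.17. With term three times as frequent it is 3.07–3.09.

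So the prior would be too spread out for term disease and, on average, at least about 2-fold too low.

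**3. Double counting, if the ratios are unconditional.**

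The article gives no correlation between first-trimester and later values, so rho is assumed. Take one marker read twice, each reading separating cases by d SD, with correlation rho given outcome.

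- Product of separate ratios: log LR = d(x₁ + x₂) − d².
- Correct joint ratio: log LR = [d(x₁ + x₂) − d²]/(1 + rho).
- The calibration slope of the product is therefore 1/(1 + rho).

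| rho (assumed) | Slope, unconditional | Simulated | Simulated, conditional on first reading |
|---|---|---|---|
| 0 | 1.00 | 0.99 | 0.99 |
| 0.3 | 0.77 | 0.77 | 1.00 |
| 0.5 | 0.67 | 0.66 | 1.00 |
| 0.7 | 0.59 | 0.59 | 1.00 |

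For a single woman with d = 1 and both readings at +2 SD, the product is exp(3) = 20.1. The joint ratio is exp(3/1.3) = 10.1, exp(3/1.5) = 7.4 or exp(3/1.7) = 5.8, so her odds would be overstated 2.0-, 2.7- or 3.4-fold. Conditioning removes the problem at every correlation tested (0 to 0.8; slopes 0.99–1.01).

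**The case against.** The best reply is that the article states neither fault. It refers to an FMF risk estimate without saying which one, and never says that the preterm risk is carried over to term preeclampsia. It does not call the likelihood ratios unconditional; MCMC is compatible with a joint or conditional likelihood, and simple multiplication of odds would not need it. The derivation of the ratios may be set out in a fuller plan that is not shown. Logistic regression is the primary method, and all models are to have cross-validated calibration slope and intercept. Augmentation index and ophthalmic artery Doppler are listed only at the later windows and repeat nothing in the prior.

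Much of this stands, and it rules out three stronger readings that a reader might infer:

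- *That the plan prescribes the preterm risk as prior for term preeclampsia.* This is an inference from the objectives and Table 1. The Introduction reports FMF performance for term disease, so a term-specific estimate may be obtainable, although none is listed as recorded.
- *That the posteriors in general are for the wrong outcome.* Only term preeclampsia at 35–36 weeks lacks a listed matching prior.
- *That both faults make the posteriors overconfident.* Double counting makes them too extreme. The outcome mismatch chiefly makes the average term risk too low.

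Nor is re-measuring a marker a fault in itself: a later reading is new data and is properly used through a conditional ratio.

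The reply does not dispose of the point. The article fixes the prior and names only the later measurements as the source of the ratios, and MCMC does not itself supply conditioning. The calibration checks would detect the miscalibration, but no recalibration step is stated.

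**Conclusion.** The point holds in conditional form. The described update neither matches the prior to the outcome nor conditions the likelihood ratios on the values already in it. If the recorded preterm risk is used for term preeclampsia at 35–36 weeks, the result is a risk for the wrong event, at least about 2-fold too low on average; this rests on the article's statement of relative frequency and on a prior calibrated for preterm disease. If the ratios for MAP, UtAPI and PlGF are unconditional, posteriors are too extreme, with illustrative slopes of 0.77 to 0.59 for correlations of 0.3 to 0.7. Those correlations and the equal-information model are assumptions; at zero correlation given outcome there is no double counting. The point concerns an additional analysis under the primary objectives and should be settled before that analysis is run.

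**What to change.** Amend the Bayesian updating text as follows.

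1. State the outcome of each prior and use only a matched one: the preterm-preeclampsia risk for preterm preeclampsia, and the FGR risk for FGR. For term preeclampsia at 35–36 weeks, use a term-specific first-trimester risk or a baseline risk estimated in the cohort.
2. Restrict each update to women with a recorded first-trimester risk (enrollment is open at any stage before 37 weeks) who are undelivered and undiagnosed at that visit, and make the prior refer to them.
3. Either make the likelihood ratios for repeated markers conditional on their 11–13 week values, and at 35–36 weeks on the 26–28 week values too, or fit a Bayesian logistic model. That model would take logit(FMF risk) with estimated intercept and slope and enter early and later marker values jointly. The first option keeps the planned method; the second also recalibrates the prior.

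The cost is a change of wording and a standard model using variables the study already collects, plus a term-specific risk if that option is chosen. There will be a few more parameters to estimate and fewer eligible women than in the whole window dataset.

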**Methods:**

The Placental Health Study is a prospective cohort study conducted at the Maternal Fetal Medicine Unit at Gold Coast University Hospital, Australia. Singleton pregnancies are enrolled at 11 to 13 weeks, 26 to 28 weeks, and 35 to 36 weeks of gestation and are followed until delivery. Exclusion criteria are multiple pregnancies, major fetal anomalies, maternal age below 18 years, and inability to provide informed consent. Clinical data, standardized ultrasound and Doppler measurements, hemodynamic parameters, and biospecimens (serum, plasma, whole blood RNA, and urine) are collected at each visit. Three gestational age-specific datasets (11‐13 weeks, 26‐28 weeks, and 35‐36 weeks) will be constructed for model development. Prediction models will be developed using multivariable logistic regression. Competing risks (Fine and Gray) models will be used as sensitivity analyses for outcomes related to gestational age at delivery. Bayesian updating will be applied to refine existing Fetal Medicine Foundation risk estimates using additional biomarkers or variables collected later in pregnancy. Developed models will undergo internal validation via 5-fold cross-validation, with performance assessed through model discrimination, calibration, and comparison against existing approaches. Collected biospecimens will also be analyzed for angiogenic markers and exploratory omics studies.

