Model discrimination: AUC-ROC and c-statisticCalibration assessment: calibration plots and calibration slope and intercept on cross-validated dataClinical utility: sensitivity, specificity, positive and negative predictive values, and screen-positive ratesComparison against existing risk assessment methods: NICE and ACOG guidelines for preeclampsia risk scoring

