## Discussion

This protocol describes a prospective cohort study aimed at developing advanced prediction models for placental dysfunction–related pregnancy complications, allowing for dynamic and personalized accurate risk assessment throughout the pregnancy. First- and second-trimester prediction models aim to enhance early risk assessment for placental dysfunction–related complications (preeclampsia, FGR, preterm birth, and stillbirth), and the third-trimester model focuses on predicting the onset of term complications (preeclampsia and FGR) and determining optimal delivery timing. This comprehensive strategy advances personalized obstetric care through evidence-based risk stratification.

The FMF first-trimester prediction model shows superior performance compared with traditional risk-factor–based checklists [17]. By combining maternal factors with measurements of MAP, UtAPI, and serum PlGF, this model is the most effective method for predicting early-onset and preterm preeclampsia, achieving detection rates of 90% and 75%, respectively [22,43]. This model has been validated across diverse populations, consistently demonstrating predictive performance comparable to the original studies and has been tested in randomized clinical trials [24,44-48]. Importantly, when coupled with prophylactic low-dose aspirin administration starting before 16 weeks’ gestation in high-risk pregnancies, this screening strategy reduces preterm preeclampsia by more than 60% [24,49]. In addition, the model achieves detection rates of 56% for early SGA fetuses (<32 weeks) and 46% for preterm SGA neonates (<10th percentile), with aspirin use potentially reducing the incidence of preterm SGA by 20% and early SGA by 40% [23].

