These advancements in preterm preeclampsia screening have prompted updates to national [50,51] and international [52] guidelines, recommending implementation of the prediction model with prophylactic low-dose aspirin to reduce preterm preeclampsia incidence and associated adverse outcomes. A cost-effectiveness analysis in Australia demonstrated significant benefits of this screening strategy, including prevention of 31 preterm preeclampsia cases and cost savings of approximately Aus $1.43 million (Aus $1=US $0.72 as of August 27, 2020) over a 2-year period [53]. Despite these clinical benefits, the FMF first-trimester prediction model has not yet become a standard component of routine maternity care for all health care providers in Australia. Gold Coast University Hospital has implemented FMF-based first-trimester preeclampsia screening in routine clinical care, providing a valuable setting to generate evidence supporting broader application in clinical practice.

Current prediction models still have limited accuracy for predicting term preeclampsia and SGA due to their complex etiology. Although considered less severe, term complications constitute most cases, occurring at least twice as frequently as preterm preeclampsia, and impose a significant health care burden [26]. While the first-trimester screening combined with low-dose aspirin effectively prevents preterm preeclampsia, it showed limited efficacy for term preeclampsia [24]. A prediction model at 35 to 36  weeks’ gestation, using maternal factors and biomarkers, can identify approximately 70% of pregnancies at risk of developing term preeclampsia [54]. In addition, planned birth at term is a potential prevention strategy for term preeclampsia [55,56]. A recent secondary analysis from a prospective nonintervention cohort study has demonstrated that a risk-stratified approach based on a combined prediction model at 35 to 36  weeks’ gestation with timed birth is likely able to reduce the risk of term preeclampsia [27]. However, research on individualized risk assessment models at late gestation to determine optimal delivery timing remains limited. This cohort study will facilitate the development of refined prediction models and optimal delivery timing strategies to reduce term preeclampsia incidence and improve pregnancy outcomes.

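### The new models are compared only with the NICE and ACOG preeclampsia checklists, so the plan cannot show improvement on the FMF model it sets out to improve, and FGR has no named comparator

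*Protocol article*

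**What the plan says.** - **Comparator.** The performance list that closes Primary Objectives: Prediction Model Development asks for a comparison "against existing risk assessment methods: NICE and ACOG guidelines for preeclampsia risk scoring". Nothing marks the two guidelines as examples. The abstract is generic: "performance assessed through model discrimination, calibration, and comparison against existing approaches".
- **Aim.** The first primary objective begins "To improve current predictive models or develop new predictive models for placental dysfunction–related pregnancy complications". The analysis section names the model to be improved: "To further improve upon current FMF prediction models, a Bayesian updating approach will be applied to refine existing FMF first-trimester risk estimates". There the FMF risk serves as the prior.
- **Standing of FMF.** The Discussion states "The FMF first-trimester prediction model shows superior performance compared with traditional" checklists based on risk factors. It adds: "Gold Coast University Hospital has implemented FMF-based first-trimester preeclampsia screening in routine clinical care".
- **Data.** Table 1 in Results lists, under the 11-13 week assessment, "FGR risk, and preterm preeclampsia risk".

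**The concern.** A claim of improvement needs the model being improved as its reference. By the article's own account, the checklists are weaker than FMF and FMF is current practice at the site. Beating the checklists would repeat a result the article already treats as known. It would leave open whether added Doppler, hemodynamic or biomarker measurements gain anything over existing screening.

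FGR is worse placed. The two guidelines are listed for preeclampsia scoring only, so the list offers no existing method to set beside the FGR models.

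**Working it through.** **1. Is FMF a comparator anywhere?**

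| Place | Role of FMF |
|---|---|
| Abstract, Methods | Risk estimates to be refined; comparators described only in general terms |
| Prediction Model Development, logistic models (primary approach) | None stated |
| Prediction Model Development, Bayesian updating | Prior, updated with 26-28 and 35-36 week measurements |
| Performance list | Not named |

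At 11-13 weeks, the window in which the FMF model operates, it has no stated analytic role. For the Bayesian update, no comparison of prior with posterior performance is stated. So neither the general wording in the abstract nor the use of FMF as prior supplies the missing comparison.

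**2. What is the AUC of 0.75?** Sample Size Estimation gives 10% incidence of a composite (preeclampsia and SGA or FGR), up to 15 predictors, AUC 0.75 and about 1700 participants. The shrinkage criterion for a binary prediction model reproduces that total:

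n = P / [(S − 1) ln(1 − R²/S)]

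Here P = 15 and S = 0.9 (assumed; not stated). R² is 0.0747 to 0.0748, simulated from AUC 0.75 at 10% prevalence. For R² = 0.07485: ln(1 − 0.07485/0.9) = −0.0868, so n = 15/0.00868 = 1728. For R² = 0.07471, n = 1732. Both are within 2% of 1700. The 0.75 is thus an input to the sample size for the composite. It is neither an acceptance level nor a figure for preterm preeclampsia.

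**3. Can the gap be sized?** Assume an equal-variance binormal ROC curve and treat a 10% screen-positive rate as a 10% false-positive rate:

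AUC = Φ[(z(detection) + z(0.90))/√2]

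- FMF, preterm preeclampsia, 75% (Introduction): Φ[(0.674 + 1.282)/1.414] = 0.92.
- FMF, term preeclampsia, 41% (Introduction): Φ[(−0.228 + 1.282)/1.414] = 0.77.
- Conversely, AUC 0.75 gives detection Φ(0.954 − 1.282) = 37%, or about 32% at a 10% overall screen-positive rate with 10% prevalence.

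Beside 37%, FMF is 38 points ahead (75 − 37) or 4 points ahead (41 − 37), depending on the outcome chosen, and neither outcome is the composite. The lower edge of the gap is unknown because no checklist detection rate is given. If the checklists detected 30% to 60% of preterm preeclampsia (assumed), the band in which a model beats them and loses to FMF would be 75 − 30 = 45 down to 75 − 60 = 15 points wide. The existence of the band follows from the article's statement that FMF is better; its width does not.

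**4. How precise would an FMF comparison be?** Results reports 1072 completed pregnancies. If preterm preeclampsia occurs in 1% to 3% (assumed), that is 1072 × 0.01 ≈ 11 to 1072 × 0.03 ≈ 32 cases. A single detection rate of 75% would then have a 95% half-width of 1.96 × √(0.75 × 0.25/11) = 26 points, or 15 points with 32 cases. Restricting to women with a recorded first-trimester risk can only reduce the case count.

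**The case against.** Several points on the other side stand.

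- The first primary objective is to improve current models or to develop new ones. The comparison fails only the first limb.
- A reader might infer that a model at AUC 0.75 would find about half the cases FMF finds and still beat the checklists. The document does not support this. It sets a composite-outcome input beside a preterm preeclampsia figure. A 37% model would also beat the checklists only if they detect less than 37%, which is not stated.
- A reader might infer that every woman already has a stored FMF risk. Recruitment and Retention allows entry at any stage before 37 weeks, and Table 1 lists the risks only under 11-13 weeks and does not label them FMF. Availability can be inferred only for women in the Bayesian update, which needs that risk as its prior.
- A poor model would be partly visible anyway. Sensitivity at screen-positive rates such as 10% is planned, and the Introduction quotes FMF detection at 10%. That is a comparison across different women, however, and does not replace a paired one.
- Misreporting is a possibility, not a certainty, since no rule for claiming improvement is stated.

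The argument that a condensed article may leave comparators to a fuller plan does not carry. The article does state its comparators, and by its own account omits the stronger one.

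**Conclusion.** The point holds in limited form. As written, the comparison cannot show whether the new models improve on FMF, and FGR has no named comparator. This rests on the text alone. Its practical size is undetermined: a model between checklist and FMF performance would look like an improvement, but how wide that range is cannot be derived from the document. The binormal figures and the 30% to 60% checklist range are illustrations under stated assumptions.

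The document does not support saying that the study will report a worse model as better, or that the whole primary objective goes unanswered. The change is cheap and should be made before the final models are fitted.

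**What to change.** In the performance list:

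1. Name the first-trimester FMF risk (the one already used as the Bayesian prior) as main comparator for preterm preeclampsia and FGR at 11-13 weeks, and carry it forward at 26-28 weeks. Include prior versus posterior for the Bayesian update.
2. Restrict this comparison to women with a recorded first-trimester risk and report how many there are.
3. In those women, report paired differences in cross-validated AUC and in detection at a fixed 10% screen-positive rate, with confidence intervals. Report calibration separately: recalibrating FMF is a monotone transformation and changes neither of these two measures.
4. State that treatment prompted by FMF screening (for example aspirin, if given) may lower FMF's apparent detection and so favor the new models. Table 1 records medication, so show results with recorded treatment taken into account.
5. At 35-36 weeks, compare with the published model cited in the Discussion only if it can be computed from the collected variables.
6. Keep NICE and ACOG as secondary comparators, and do not claim improvement over current practice from the checklist comparison alone. A rule that the interval must exclude zero is not advised: with so few cases it would mainly test power.

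The cost is wording and analysis code. The downsides are a smaller reported gain, a comparison limited to a subset, and wide intervals for rare outcomes.
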